### Trial design

2.1

We will conduct a single-centre, open-label, randomised controlled trial. Patients diagnosed with BSP receiving BoNT treatment at our centre will be approached. The protocol follows the Standard Protocol Items: Recommendations for Interventional Trials guidelines (22). Outcomes, including symptom severity, disability, and quality of life, will be evaluated at baseline and at weeks 2, 4, 8, 12, 16, 20, and 24 post intervention. Patients will be asked to complete a self-report questionnaire to document their response to BoNT and the duration of clinical benefits after BoNT treatment. We will recruit only those patients who have received positive benefits from BoNT for less than 12 weeks. We plan to enroll 64 patients and randomly (1:1) assign them to the experimental group (topical FEO combined with BoNT-A injection) or control group [topical coconut oil (CO) combined with BoNT-A injection]. CO will be used as the control because FEO must be diluted 1:1 with CO as the carrier oil (16).

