**Figure 1 fig1:**
[figure not shown]
Clinical trial flow diagram. BoNT-A, botulinum toxin type A; CO, coconut oil; FEO, frankincense essential oil; MRI, magnetic resonance imaging; PEGR, Patient Evaluation of Global Response.

**Table 1 tab1:** Overview of the study.

Item	Description
Study title	Efficacy and safety of combination of frankincense and botulinum toxin in the treatment of blepharospasm: a protocol for a single-centre, open-label, randomized, controlled trial
Study design	A single-centre, open-label, randomized, controlled trial will be conducted in 64 eligible BSP patients, and they will be randomly assigned (1:1) into the experimental group (topical FEO combined with BoNT) and control group (topical CO combined with BoNT) for the 24-week follow-up.
Primary endpoint	The symptom improvement over a 24-week follow-up period.
Secondary endpoints	Intervals between the last and the next BoNT treatments; Improvement rates in motor symptom severity (JRS, BSRS, and BFMDRS scores); Improvement rates in the quality of life (BSDI, SF-36, and CDQ-24 scores); Patient subjective efficacy evaluation (PEGR scores); Incidence of adverse events.
Research intervention(s)/Investigational agent(s)	Daily application topical FEO the day after BoNT injection in the experimental group. Daily topical application of CO the day after BoNT injection in the control group. Outcomes will be collected at baseline and different follow-up time points. BoNT: Hengli. FEO/CO: Aromatics International.
Study population	Patients aged 18 to 70 years whose efficacy duration of BoNT injection was less than 12 weeks.
Sample size	64
Study duration for individual participants	24 weeks

BFMDRS, Burke Fahn Marsden’s Dystonia Rating Scales; BoNT, botulinum toxin; BSDI, Blepharospasm Disability Index; BSP, blepharospasm; BSRS, Blepharospasm Severity Rating Scale; CDQ-24, Cranio-cervical Dystonia Questionnaire; CO, coconut oil; FEO, frankincense essential oil; JRS, Jankovic Rating Scale; SF-36, Short Form-36 Health Survey; PEGR, Patient Evaluation of Global Response.

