### Trial assessment and follow-up

2.9

Full eligibility criteria will be assessed and confirmed before randomization. Further assessments should be conducted at multiple time points. An overview of the data collection process is provided in Table 2. Data will be collected from all participants until they complete the 24-week follow-up period or discontinue the study.

**Table 2 tab2:** Time and events.

Description	Screening	Day 0	2nd week	4th week	8th week	12th week	16th week	20th week	24th week
Consent	**√**								
Neurological exam	**√**								
Medical history	**√**								
Inclusion/exclusion	**√**								
Randomization	**√**								
MRI	**√**								
Baseline assessment	**√**								
Motor symptom assessment	**√**		**√**	**√**	**√**	**√**	**√**	**√**	**√**
Quality-of-life assessment	**√**		**√**	**√**	**√**	**√**	**√**	**√**	**√**
Video recording	**√**		**√**	**√**	**√**	**√**	**√**	**√**	**√**
PEGR			**√**	**√**	**√**	**√**	**√**	**√**	**√**
Non-motor symptom assessment	**√**					**√**			**√**
Blinded rater evaluation	**√**	**√**	**√**	**√**	**√**	**√**	**√**	**√**	**√**
BoNT injection		**√**							
FEO/CO application			**√**	**√**	**√**	**√**	**√**	**√**	**√**
Clinical assessments	**√**	**√**	**√**	**√**	**√**	**√**	**√**	**√**	**√**
Safety assessment	**√**	**√**	**√**	**√**	**√**	**√**	**√**	**√**	**√**

BoNT, botulinum toxin; CO, coconut oil; FEO, frankincense essential oil; MRI, magnetic resonance imaging; PEGR, Patient Evaluation of Global Response.

Patients will be withdrawn for the follow-up during a 24-week observation period if they meet any of the following three conditions: (1) the subject receives a BoNT-A reinjection during the follow-up period, (2) the JRS score returns to the baseline score, or (3) completion of a 24-week follow-up visit.

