### Statistical analysis

2.10

Trial analysis will be performed on an intention-to-treat (ITT) population. No interim analyses will be performed. A full statistical analysis plan will be developed before the final analysis.

Assumptions for parametric tests will be evaluated before analysis. Normality will be assessed using the Shapiro–Wilk test and Q-Q plots, and homogeneity of variances with Levene’s test. If these assumptions are not met, non-parametric alternatives will be used.

Missing data will be handled under the ITT principle, using all available observations without imputation beyond the last completed visit. Mixed-effects models will be used for repeated-measures secondary outcomes under the missing-at-random assumption. A per-protocol sensitivity analysis will also be conducted.

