#### Secondary endpoint analysis

2.10.3

Secondary outcome metrics include the interval between BoNT treatments, improvement rates in motor symptoms (JRS, BSRS, and BFMDRS), quality of life (BSDI, SF-36, and CDQ-24), and subjective efficacy evaluations (PEGR) at different time points. The interval between BoNT-A treatments will be expressed as mean ± SD with differences analyzed using the two-sample t-test if the data follows a normal distribution; otherwise, median and interquartile range will be used, and the Mann–Whitney U-test will be applied. Improvement rates in motor symptoms, quality of life scores, and subjective efficacy evaluations will be expressed as mean ± SD or median and IQR, depending on the normality distribution. Differences between the two groups and their 95% CI will be reported. Outcomes with repeated-measures continuous data will be compared between the groups using repeated-measures ANOVA. Multiple tests will be corrected using Bonferroni correction. All statistical analyses will be performed using SPSS v.25.0 (IBM Corp). *p* < 0.05 will indicate a statistically significant difference.

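### Follow-up ends at reinjection or return of the JRS score to baseline, which conflicts with secondary outcomes planned to week 24 and with the BoNT-interval endpoint

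*Protocol article*

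**What the plan says.** Section 2.9 lists three conditions that end a patient's follow-up. The first two are "1) the subject receives a BoNT-A reinjection during the follow-up period, (2) the JRS score returns to the baseline score"; the third is completing week 24. The same section says "Data will be collected from all participants until they complete the 24-week follow-up period or discontinue the study".

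Other parts of the article assume observation to week 24:

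- Section 2.1 says that severity, disability and quality of life "will be evaluated at baseline and at weeks 2, 4, 8, 12, 16, 20, and 24 post intervention". Section 2.4 and Table 2 repeat this schedule and add PEGR, safety and, at weeks 12 and 24, the non-motor scales.
- Section 2.3 states its quality-of-life, self-rating and safety hypotheses at the 24-week follow-up.
- Table 1 lists "Intervals between the last and the next BoNT treatments" as a secondary endpoint, and section 2.10.3 confirms it: "Secondary outcome metrics include the interval between BoNT treatments". The planned analysis is "The interval between BoNT-A treatments will be expressed as mean ± SD with differences analyzed using the two-sample t-test", or the Mann–Whitney test if the data are not normal. Censoring is not mentioned.
- Section 2.10 says "Trial analysis will be performed on an intention-to-treat (ITT) population", with missing data handled by "using all available observations without imputation beyond the last completed visit" and a mixed model under missing at random. Section 2.10.3 names repeated-measures ANOVA for the same kind of outcome.

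**The concern.** The event that defines the primary outcome, loss of benefit, also ends observation for every other outcome. For a duration endpoint that does little harm. For outcomes compared visit by visit, the patients present at a late visit are those whose benefit lasted long enough to get there. If FEO works as hypothesised, that selection differs between the arms.

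Three things are at stake: the secondary comparisons after week 12, the interval to the next BoNT treatment (which needs a date that may fall after the patient has left), and adverse-event counts, because the arm with longer benefit is watched for longer.

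There is also a wording problem. The exit rule refers to the JRS score without saying which, while the primary endpoint uses the JRS severity score. Section 2.2 shows that the scale has a separate frequency sub-score, so the two rules need not be triggered at the same time.

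**Working it through.** **Inputs (section 2.6).** Control duration of benefit 75 ± 15 days. FEO 90 ± 18.5 days, described as a mix of 50% responders at 105 ± 15 and 50% non-responders at 75 ± 15. Recruited: 32 per arm. Visits at days 14, 28, 56, 84, 112, 140 and 168.

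**The plan's own figure.** A two-sample t-test with difference 15, SD 18.5 in both arms, two-sided 0.05 and n = 25 per group has power 0.802 (n = 24 gives 0.785), so the stated 25 is reproduced. With 20% loss, 25 / 0.80 = 31.25, rounded up to 32. These planning figures can therefore be used to test the exit rule.

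**Patients seen at each visit.** I assume normal durations, JRS return at the end of benefit, no other dropout, and that the visit detecting the return is recorded. A patient then has data at a visit if the duration D exceeds the day of the previous visit, d.

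- Control: P = 1 − Φ((d − 75)/15)
- FEO, mixture: P = ½[1 − Φ((d − 75)/15)] + ½[1 − Φ((d − 105)/15)]
- FEO, single normal: P = 1 − Φ((d − 90)/18.5)

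Example, week 16 (d = 84). Control: 1 − Φ(0.6) = 0.2743, × 32 = 8.8. FEO mixture: ½(0.2743 + 0.9192) = 0.5967, × 32 = 19.1.

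| Visit | d | Control seen | FEO seen, mixture | FEO seen, N(90, 18.5) |
|---|---|---|---|---|
| Week 12 | 56 | 28.7 | 30.3 | 30.9 |
| Week 16 | 84 | 8.8 | 19.1 | 20.1 |
| Week 20 | 112 | 0.2 | 5.2 | 3.7 |
| Week 24 | 140 | 0.0 | 0.2 | 0.1 |

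Both FEO shapes are shown because an equal mix of these two groups has SD √(15² + 15²) = 21.2, not 18.5. The choice does not change the conclusion.

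**Still in benefit on the visit day** (D greater than that visit's own day). Week 16: control 0.2, FEO mixture 5.2. So of the 8.8 and 19.1 patients seen at week 16, most have just lost benefit.

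**What the analyses can do.** Repeated-measures ANOVA in its usual complete-case form keeps only patients with every visit, which at week 24 is 0.0 and 0.2. The mixed model uses all rows, but with 0.2 control patients at week 20 and none at week 24 its late contrasts are extrapolation.

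**BoNT interval.** It is observed if reinjection happens before the JRS return is recorded. If the return is recorded first, the patient leaves and no section provides for obtaining the later date. Section 1 puts reinjection after 12 weeks or at 4–5 times a year, that is, every 365/5 = 73 to 365/4 = 91 days. A return at the control mean of 75 days would be recorded at the week 12 visit, day 84, inside that range. Losses are therefore to be expected, but the order of the two events, and so the share lost, cannot be computed.

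**Observation time for adverse events.** If exit is on the day of return: 75 vs 90 days, ratio 1.20. If exit is at the detecting visit, the mean is the sum of visit gaps times the proportion seen:

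- Control: 14 + 14 + 28 × (0.9991 + 0.8974 + 0.2743 + 0.0068) = 89.0 days
- FEO mixture: 14 + 14 + 28 × (0.9996 + 0.9484 + 0.5967 + 0.1636 + 0.0049) = 104.0 days

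Ratio 1.17. Observation is 17–20% longer on FEO.

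**The case against.** Following patients until the event is a natural design for a duration endpoint, and here the event that ends follow-up also supplies the outcome. That stands: the primary analysis is largely untouched.

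Four stronger readings are tempting, and the document does not support them.

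- *Late visits show only patients who still benefit.* Not if the detecting visit is recorded: most patients seen at week 16 have just lost benefit. The selection is on benefit at the previous visit.
- *The late contrasts are necessarily biased.* Exit triggered by an observed JRS score is compatible with missing at random for JRS, which is what the mixed model in section 2.10 assumes. For JRS under that model the demonstrable problem is lack of data and extrapolation. The repeated-measures ANOVA in section 2.10.3 lacks this defence.
- *Intention-to-treat cannot be honoured.* It can for the primary endpoint, where every patient who leaves through JRS return contributes a duration.
- *The BoNT interval is unobtainable.* The first exit condition itself expects reinjections during follow-up, patients are treated at the trial centre, and nothing forbids recording a later date. What can be said is that no provision for it is stated.

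The exit rule's JRS score may also be shorthand for the severity score. It is an ambiguity to resolve, not a demonstrated effect.

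**Conclusion.** The concern holds for the secondary and safety outcomes. The exit rule in section 2.9 contradicts the week-24 schedule and hypotheses. On the protocol's own planning figures, week 16 compares about 9 control with 19–20 FEO patients selected on benefit at week 12, week 20 compares essentially no control patients with 4–5 FEO patients, and week 24 is empty. The 24-week secondary hypotheses in section 2.3 and the week-24 non-motor comparison cannot be tested as planned. An unknown share of BoNT intervals will be missing, and adverse events are observed 17–20% longer on FEO.

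The counts rest on normal durations, JRS return coinciding with end of benefit, and no other loss. Longer real durations would fill the late visits somewhat but would not remove the selection.

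A reader should not extend this to the primary endpoint. It needs only that the JRS score in the exit rule be reconciled with the JRS severity score in the endpoint definition.

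**What to change.** Amend section 2.9 so that end of benefit and end of follow-up are separate.

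1. For every randomised patient, record to week 24 the date of return of the JRS severity score and the date of the next BoNT injection, as events. State which JRS score the exit rule means.
2. Analyse the BoNT interval as time-to-event, censored at week 24, in place of the t-test or Mann–Whitney test.
3. Choose one of two courses for the secondary outcomes. Either keep the Table 2 visits after benefit ends, with a stated strategy for data collected after reinjection; or, if early exit stays, limit between-group secondary comparisons to visits up to week 12 and withdraw the 24-week secondary claims.
4. Name one repeated-measures method; sections 2.10 and 2.10.3 currently name two.
5. Report adverse events per unit of observation time.

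The cost is a protocol amendment and, under the first course, some attendance after benefit has ended. The visits are already listed in Table 2. Scores after reinjection reflect a second BoNT cycle, so the strategy for them must be fixed in advance. Treatment decisions are unchanged. Section 2.7 has recruitment running to February 2027, and outcomes not collected after exit cannot be recovered by a later analysis plan, so the amendment should come soon.

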### Statistical analysis

2.10

Trial analysis will be performed on an intention-to-treat (ITT) population. No interim analyses will be performed. A full statistical analysis plan will be developed before the final analysis.

Assumptions for parametric tests will be evaluated before analysis. Normality will be assessed using the Shapiro–Wilk test and Q-Q plots, and homogeneity of variances with Levene’s test. If these assumptions are not met, non-parametric alternatives will be used.

Missing data will be handled under the ITT principle, using all available observations without imputation beyond the last completed visit. Mixed-effects models will be used for repeated-measures secondary outcomes under the missing-at-random assumption. A per-protocol sensitivity analysis will also be conducted.

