### Data measurements

2.4

All subjects will undergo MRI before the clinical intervention. Demographics, clinical characteristics, and severity of BSP will be recorded using blepharospasm severity scales. The severity of BSP, quality of life, and self-rating of response to efficacy will be evaluated in each patient at baseline and at weeks 2, 4, 8, 12, 16, 20, and 24 after therapy. Moreover, a 5-min standardised video recording of the facial area will be conducted to assess and document the blink rate and duration of sustained eyelid closure (26). In addition, all subjects will be evaluated with non-motor symptom scales at baseline, at weeks 12 and 24 weeks after the intervention, using the Mini-Mental State Examination (MMSE) (31), Hamilton Rating Scale for Anxiety (HAMA) (32), Hamilton Rating Scale for Depression (HAMD) (33), Yale-Brown Obsessive-Compulsive Scale (Y-BOCS) (34), and the Pittsburgh Sleep Quality Index (PSQI) (35). All evaluations applied in the study will be performed at each visit by two evaluators who will be blinded to the clinical information and group assignments of the participants. This will safeguard the objectivity of the evaluation process and ensure the consistency and validity of the assessment results. Figure 1 illustrates the flowchart of the clinical trial procedure, and Table 1 presents an overview of the study.

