### Sample size

2.6

The sample size was calculated using the two-sample t-test method in PASS 15 software (NCSS, LLC, Kaysville, Utah, USA), with a two-sided significance level of 0.05 and a power of 0.8. Based on preliminary clinical observations obtained in our center, topical FEO alone was effective in approximately 50% of patients with BSP. This finding, combined with a conservative estimate of efficacy, prompted a reassessment of the required sample size to ensure adequate statistical power. The revision was implemented after trial initiation but prior to completion of participant recruitment, and constitutes an important protocol modification based on internally generated data. To determine the mean and standard deviation (SD) needed for the sample size calculation, we retrospectively analysed data from 61 patients with BSP at our movement disorders clinic who had received standard BoNT-A treatment and met the study’s inclusion criteria. After receiving their last three consecutive BoNT-A injections, these patients experienced clinical benefits for less than 3 months each time, demonstrating consistently unsatisfactory therapeutic effects. The mean duration of clinical benefits was 73.99 days (SD = 14.28). Given that the control group will receive a placebo, there may have been greater variability in the therapeutic effects due to individual response and disease progression; therefore, we decided to round the mean value to 75 days and the SD to 15 (i.e., 75.0 ± 15.0) to ensure robustness in the calculation. In this study, we hypothesized that combining BoNT-A injection with topical FEO would extend the effective duration of symptom relief by 30 days to 105.0 ± 15.0 days. Given an expected effective rate of only 50%, we estimated the mean duration of benefit in the experimental group as 90.0 ± 18.5 days, reflecting a weighted average between responders and non-responders. The resulting sample size calculation indicated N1 = N2 = 25, meaning that 25 participants are required for each group. Considering the participant loss to follow-up, we determined that each group would recruit 32 participants. A professional statistician verified the sample size calculation method. The amended protocol was reviewed and approved by the Ethics Committee of the First Affiliated Hospital of Sun Yat–sen University.

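### The primary test is left to a pre-test on the trial data; if duration is read from the visits, that pre-test will practically always select Mann-Whitney, and power at 25 per arm is about 70–79%, mainly because of the 4-week visit grid

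*Protocol article*

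**What the plan says.** Four places in the protocol article bear on this.

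- **Sample size (2.6).** "The sample size was calculated using the two-sample t-test method in PASS 15 software", "with a two-sided significance level of 0.05 and a power of 0.8". The planning figures are in days: control 75 with SD 15, rounded from a retrospective mean of 73.99 (SD 14.28) in 61 clinic patients. For the experimental arm, "we estimated the mean duration of benefit in the experimental group as 90.0 ± 18.5 days". The result is 25 per group, raised to 32 for loss to follow-up.
- **Data measurements (2.4), also Trial design (2.1) and Table 2.** Severity "will be evaluated in each patient at baseline and at weeks 2, 4, 8, 12, 16, 20, and 24 after therapy". From week 4 onward the visits are 28 days apart.
- **Statistical analysis (2.10).** Normality is judged by Shapiro-Wilk and Q-Q plots, and equality of variances by Levene's test. "If these assumptions are not met, non-parametric alternatives will be used".
- **Primary endpoint analysis (2.10.2).** Duration of relief on the JRS severity subscale is compared by a t-test or a Mann-Whitney test, and a difference with its 95% confidence interval is reported.

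The article does not say how a duration in days is obtained from the visit ratings.

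**The concern.** The confirmatory test is not fixed in advance. Two tests are named, and the trial's own outcome data choose between them. Only one of the two was used to size the trial.

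The outcome scale makes this more than a formality. Improvement is defined on the JRS severity score, and no JRS rating between visits is described. Duration read from visits can take only eight values (0, 14, 28, 56, 84, 112, 140 and 168 days), while the planned effect is 15 days. Data this heavily tied will not pass a normality test, and the coarse scale costs power whichever test is used. The stated 80% would then belong to a measurement scale, and in practice a test, that the trial does not use.

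The variance branch has a separate weakness. The Sample size section itself expects unequal spread (SD 15 against 18.5), because only about half of the experimental arm is expected to respond. A Levene rejection sends the analysis to Mann-Whitney, which is not a remedy for unequal variances.

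**Working it through.** **Inputs (Sample size, 2.6).** Two-sided alpha 0.05; difference 90 − 75 = 15 days; SD 15 (control) and 18.5 (experimental). Behind the experimental figure is a 50:50 mix of non-responders at 75 ± 15 and responders, for whom the treatment would "extend the effective duration of symptom relief by 30 days to 105.0 ± 15.0 days".

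**Step 1: reproduce the plan's figure** ("The resulting sample size calculation indicated N1 = N2 = 25"). Power comes from the noncentral t distribution with noncentrality (15 / SD) × √(n/2) and 2n − 2 degrees of freedom.

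- SD 18.5 in both arms: n = 24 gives 78.5%. At n = 25 the noncentrality is (15/18.5) × √12.5 = 2.87 and power is 80.2%. This reproduces N = 25.
- SDs 15 and 18.5 as written: 80.3% already at n = 21, and 87% at n = 25.
- The mixture: its SD is √(15² + 15²) = 21.2. With 15 in control the root-mean-square SD is √((225 + 450)/2) = 18.4, and power at n = 25 is about 81%.

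All three are carried forward, because the article does not say which SD entered the software.

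**Step 2: what the grid does to the shape.** Take control durations as N(75, 15). The probability of falling between the week 8 and week 12 visits (56 to 84 days) is Φ(0.60) − Φ(−1.27) = 0.726 − 0.103 = 0.62. About 16 of 25 control patients would share one recorded value.

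**Step 3: what the grid does to the t-test.** Recording on a 28-day grid adds roughly 28²/12 = 65.3 to the variance. With SD 18.5 in both arms, √(342.3 + 65.3) = 20.2, the noncentrality falls to (15/20.2) × √12.5 = 2.63, and power is 73%. The same step gives 79% for SDs 15/18.5 and 74% for the mixture.

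**Step 4: simulation** (8,000–10,000 trials per setting, no dropout). Duration was set to the last improved visit, the first lost visit or the midpoint; ranges cover the three. The switch to Mann-Whitney was driven by Shapiro-Wilk at 0.05 in either arm.

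| SDs assumed | t-test, days, n = 25 | t-test, grid, n = 25 | Mann-Whitney, grid, n = 25 | Mann-Whitney, grid, n = 32 |
|---|---|---|---|---|
| 18.5 in both arms | 80% | 73% | 71–72% | 82% |
| 50:50 mixture, control 15 | 80% | 73–74% | 70–71% | 81% |
| 15 and 18.5 as written | 87% | 80% | 78–79% | 87–88% |

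On the grid, Shapiro-Wilk rejected in at least one arm in 100% of trials at both sample sizes, so the Mann-Whitney columns are also the power of the pre-test rule.

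**Step 5: split the loss.** From days to grid with the t-test kept, power falls by about 7 points in each row (80 to 73, 80 to 73–74, 87 to 80). From t-test to Mann-Whitney on the grid it falls by a further 1–3 points.

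**Step 6: drop the grid assumption.** With durations in exact days, Shapiro-Wilk rejects in about 10% of trials at n = 25 and the rule keeps about 80% power (SD 18.5 in both arms, or the mixture). With weekly values it rejects in about 20–25% and the rule keeps about 79% in those two settings.

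**The case against.** The strongest reply is that the grid premise is an inference. Planning is in days, reinjection is a dated event that ends follow-up, patients complete a questionnaire on duration of benefit, and deriving days from visits is ordinary detail for the analysis plan still to be written. Q-Q plots are also part of the rule, so the choice is not mechanically a Shapiro-Wilk p-value. This stands in part. With true day-level durations the problem largely disappears (Step 6). But the endpoint is defined on the JRS, which is rated at visits, and a Q-Q plot of a few tied values is a staircase that would hardly rescue normality.

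A second reply is that 32 per arm are recruited and the analysis is by intention to treat, so power may exceed 80% even on the grid. That is correct if all are evaluable. The article's own 80%, however, is attached to 25 per arm, so 25 is the like-for-like comparison.

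Four stronger readings are tempting and are not supported:

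- **That the pre-test causes the power loss.** It costs about 1–3 points. Keeping the t-test on grid data still leaves 73–80%.
- **That the t-test can never be run and power is simply 71%.** Both hold only under stated assumptions about the grid, the SDs and the number evaluable.
- **That the p-value and the reported difference must address different hypotheses.** The article does not say which difference is reported; a Hodges-Lehmann shift would be consistent with Mann-Whitney.
- **That a log-rank or restricted-mean analysis would recover the power.** This has not been established.

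**Conclusion.** The point holds in a limited form. The rule is stated, not merely left open: outcome data choose the primary test, and the sample size rests on only one of the candidates. If duration takes visit values, Mann-Whitney will practically always be selected. Power at 25 evaluable per arm is then about 70–79%: about 71% under SD 18.5 in both arms or the mixture, and 78–79% under SDs 15 and 18.5. With 32 evaluable per arm it is about 81–88%.

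The visit grid is the main cause. The test switch is a small addition, and the Levene branch is a minor but separate fault. These figures assume the article's planning means and SDs, normal or mixed-normal durations and no dropout beyond the stated numbers. This should be corrected before the final analysis; it does not undermine the trial.

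**What to change.** - Remove the normality and variance pre-test for the primary endpoint.
- Name one primary analysis in advance that estimates the difference in days, for example Welch's t-test, with the confidence interval taken from the same analysis. Welch also handles the unequal SDs that the plan expects.
- State how duration is derived from the visit ratings (last improved visit, first lost visit, midpoint or a dated event).
- Restate power for that outcome and that test at 25 per arm. On the visit grid this is about 73–80% for Welch, depending on the SDs, which should also be stated explicitly.

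The cost is wording, one calculation and a slightly lower stated power. No patients, visits or data are added. Recruitment is planned to run to February 2027 and the full analysis plan is still to be written, so the change can be made before the final analysis.
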